### Measures

#### Client characteristics

The baseline questionnaire will collect data on age, gender, ethnicity, education level, employment status and perceived financial adversity (FaHCSIA 2007). Questions also ask about health-related help-seeking in the last three months, their child’s chronic illness, health of other family members and consultations regarding their own mental health or wellbeing. Respondents will also rate their general wellbeing, physical and mental health, ability to perform tasks, their relationships with others and involvement in the community.

#### Outcome measures

##### Parental wellbeing

The Kessler Psychological Distress Scale (K10) is a 10-item screening tool to assess distress and the likelihood of a mental disorder in the responding individual (Kessler et al. 2003; Slade et al. 2011; Andrews & Slade 2001). The K10 uses a five-point rating scale asking how often in the last four weeks participants have experienced symptoms pertaining to nervousness, agitation, psychological fatigue and depression. Higher scores indicate higher levels of distress. The K10 has established validity and acceptable reliability (Andrews & Slade 2001; Centre for Population Studies in Epidemiology 2002).

##### Family functioning

The McMasters Family Assessment Device (FAD) will be used to measure family functioning (Ryan et al. 2012). The FAD identifies strengths as well as limitations in family functioning across seven dimensions including problem solving, communication, roles, affective responsiveness, affective involvement, behaviour control and general functioning (Ryan et al. 2012). Statements describe various aspects of family functioning and respondents indicate agreement on a four-point scale, with lower scores indicating better family functioning. The FAD has adequate internal and test retest reliability (Epstein et al. 1983; Miller et al. 1985) and appropriate construct and criterion validity (Miller et al. 1985; Kabacoff et al. 1990).

##### Social connectedness

The Medical Outcomes Study Social Support Survey (MOSSSS) assesses perceived availability of functional support (Sherbourne & Stewart 1991). Respondents indicate how often each kind of support is available if they need it on a five-point scale. The 19 items represent four dimensions of support: emotional/informational support, tangible support, affectionate support and positive social interaction. Higher scores indicate higher perceived support. The scale has demonstrated good internal reliability and construct validity (Sherbourne & Stewart 1991).

##### Family belief systems

Family beliefs are a construct that contributes to family resilience (Rolland & Walsh 2006; Walsh 2002; Walsh 2003). In a study designed to measure Walsh’s Family Resilience Framework, Sixbey (Sixbey 2008) developed a measure which included subscales of ‘maintaining a positive outlook’ and ‘ability to make meaning of adversity’ (Walsh 2003; Sixbey 2008). Despite limited psychometric validity (Sixbey 2008), the items were deemed appropriate for inclusion in the Parent Outpatient Survey. Data analysis will include examination of factor loadings to examine the validity of this construct in contributing to CHiRP participants’ resilience (see below).

#### Other

A follow up parent survey will measure the impact of Step 2, the booklet intervention. The questionnaire will be administered at three and six months after baseline. It will include the outcome measures as well as questions about changes to the child’s diagnosis in the past three months, questions about the acceptability of the booklet and questions to illicit participant’s self-reported knowledge, understanding and confidence to implement strategies. A follow up parent survey will also be used to assess Step 3. The questionnaire will be administered immediately following the group intervention and then six months later. The questionnaire will include the outcome measures as well as questions regarding perceived utility and acceptability of the group content and format.

### Intervention

The CHiRP intervention content and style has been informed by a literature review of interventions aimed at improving the wellbeing of families living with childhood chronic illness (Incledon et al. 2013; Hiscock et al. 2012), and consultation with the target group (including parents, children with chronic illness and siblings of children with chronic illness) and allied health and medical staff at the paediatric hospital. The intervention promotes the importance of family routines, relationship building, parenting skills, self-care, cognitive restructuring, communication, problem-solving skills and accessing social support.

#### Step 1 routine dissemination: fact sheet intervention

The Family Resilience and Wellbeing Fact Sheet is a two-sided, A4 document, produced in a style concordant with existing hospital fact sheets. The Fact Sheet provides brief psycho-education and practical resilience building strategies for families. Contact information is provided for a small number of relevant community organisations.

#### Step 2 targeted dissemination: booklet intervention

The Family Resilience and Wellbeing booklet, entitled “Strong Parents, Resilient Families” is a 73-page, A4 sized, colour illustrated spiral bound booklet. The booklet uses a parent-focussed, strengths-based, cognitive behavioural approach to promoting family resilience (Padesky & Mooney 2012). The content encourages parents to identify family strengths, develop an understanding of the characteristics of a resilient family, identify goals for skills and strengths building and practice specific strategies to improve family resilience. Parents are encouraged to complete the resilience building activities together with family members. The booklet also contains a comprehensive list of community services for families and children living with chronic illness. Table 1 provides an overview of the booklet content.

**Table 1 Tab1:** **Overview of intervention content: strong parents, resilient families booklet**

Module	Content
Introduction	• Definition of resilience
	• Simple model of family resilience
	• Instructions and summary of booklet content
	• Case study
1. Building a strong family	• Getting to know my family activity
	• Shared lives, shared milestones timeline activity
	• Family support inventory activity
2. Building a resilient family	• Resilient families factsheet
	• Family strengths checklist activity
	• Maintain routines activity
	• Looking after yourself and each other activities
	• Family communication factsheet and worksheet
	• Hints and tips for spending time together as a family
	• Positive thinking worksheets
	• Problem solving factsheet and worksheet
	• Respectful relationships factsheet/worksheet
	• Parenting tips factsheet and parenting strategies worksheet
	• Understanding an illness factsheet and self-management activity
3. Preparing for the future	• List of family support services

#### Step 3 active dissemination: parent information support group intervention

The Parent Information Support Group is an education, support and skills development group program directed toward parents experiencing psychological distress. The group program content will be based on the “Strong Parents, Resilient Families” booklet and will provide the additional benefit of an opportunity for discussion and practice of the strategies within a facilitated, interactive peer-supported environment.

Parents managing childhood chronic illness have significant demands on their time and participation in face-to-face groups can be low and attrition rates high (Stewart et al. 2012). In light of this, the information support group will combine face-to-face delivery with interactive online delivery strategies. The intervention will be conducted over six weeks. In week one, participants will attend a full day session (4 hours + 1 hour lunch) during which they will have the opportunity to connect with other parents, share their experience and interact with the facilitators to engage with the material in the “Strong Parents, Resilient Families” booklet. This session will include up to 15 participants and will be run by two trained facilitators with a background in psychology or allied health. Over weeks two to five, material pertaining to family resilience strategies will be posted once a week onto an online forum by a research team member who will act as moderator of the site. Participants will be encouraged to read the material, engage in the activity with their family, and post their comments for group online discussion. In week six, a final session will provide an opportunity for parents to meet face-to-face to discuss their experiences, review their participation in the program and complete the evaluation. A facilitator manual detailing the content, structure and format of each session and online material will maximise standardised delivery of the intervention content. Collaboration with outpatient clinic staff (e.g. Clinical Nurse Consultants or Social Workers) and carer support services will allow for delivery of the program to occur with the support of existing service providers.

### Ethics approval

CHiRP has been approved by the Hunter New England Human Research Ethics Committee (Ref No.13/03/20/4.06) and the University of Newcastle Human Research Ethics Committee (Ref No. H-2013-0157).

### Sample size

In Step 1, it is expected that the Fact Sheet will be provided to 1050 parents of children discharged from paediatric hospital services based on an estimate of inpatient numbers over a 12-month period in 2011. There will be no direct data collection from this group.

A sample size calculation was conducted to guide recruitment for Step 2, the booklet intervention. Using mean estimates based on normative scores (Andrews & Slade 2001; Kabacoff et al. 1990; Sherbourne & Stewart 1991; Sixbey 2008) and a hypothesised effect size of 0.2 as a result of receiving the family resilience and wellbeing booklet, a minimum sample of 98 participants at the three-month follow up assessment will have sufficient power (0.8) to detect a significant difference between mean scores (using alpha 0.05) in a one-sample comparison of baseline and three month follow-up data. A larger sample size will be recruited, however, to allow for attrition and sufficient numbers of participants eligible for Step 3.

In Step 3, the Parent Information Support Group intervention, using a randomised waitlist control design, the sample size will be divided randomly and equally between the group condition and the waitlist control condition. A sample size calculation used mean estimates based on a sample of Australian patients diagnosed with a mental disorder (Kohn et al. 2012) using the K10 and normative scores for the other outcome measures of interest. Effect sizes of 0.5 and 0.3 were hypothesised as a result of receiving the booklet intervention and participating in the information support group intervention or being in the control group, respectively. A sample size of approximately 120 (60 per group) participants at the three month follow up assessment will allow detection of a significant difference between mean scores using an alpha level of 0.05 in a two-sample comparison of the group condition and control condition on the outcome measures, with a power of at least 0.8.

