#### Step 2 targeted dissemination: booklet intervention

Using oneway analyses of variance (ANOVA), the relationship between demographic data (e.g. gender, age categories, ethnicity, socioeconomic level, help-seeking behaviour categories) and baseline outcome measures will be explored.

The impact of the booklet intervention will be examined using analysis of covariance (ANCOVA) to compare changes in mean scores from baseline to three-month follow-up on the outcome measures for all participants in Step 2 (n ≈ 353). To test for sustained change, a second analysis of the Step 2 participants will use a repeated measures mixed model to compare mean scores on outcome measures at baseline, three and six month follow-up for the participants who did *not* move into Step 3 (the Information Support Group Intervention phase). Further analyses will adjust for baseline characteristics to control for any confounding effects.

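### The Step 2 minimum of 98 does not follow from the stated inputs: with 0.2 as the standardised mean change, 199 are needed two-sided (156 one-sided), and 98 gives power 0.50 (0.63)

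*Protocol article*

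**What the plan says.** The Step 2 calculation is in the Sample size section of the protocol article. It starts from "Using mean estimates based on normative scores" and "a hypothesised effect size of 0.2 as a result of receiving the family resilience and wellbeing booklet". It concludes that "a minimum sample of 98 participants at the three-month follow up assessment will have sufficient power (0.8) to detect a significant difference" ("using alpha 0.05"), "in a one-sample comparison of baseline and three month follow-up data". The next sentence says that "A larger sample size will be recruited, however, to allow for attrition and sufficient numbers of participants eligible for Step 3".

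The Step 2 part of Statistical analyses then describes the baseline to three-month comparison "for all participants in Step 2 (n ≈ 353").

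The article does not say whether the test is one- or two-sided, whether 0.2 is scaled by the SD of the change or of the raw score, or what correlation between baseline and follow-up was assumed. It gives no attrition rate for Step 2.

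**The concern.** The sentence is a complete power statement: effect size, alpha, power, type of comparison and resulting n. A reader can therefore check it, and the most direct check fails by a wide margin.

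At stake is the meaning of 98. It is presented as the number at three months that is enough to test the booklet hypothesis, one of the two main hypotheses in Study aim and hypotheses. If follow-up ended near that number, the sentence could be cited as evidence of adequate power when the chance of detecting the planned effect was about one in two (two-sided). A null booklet result might then be read as more informative than it is.

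**Working it through.** **Inputs from the Sample size section:** effect size 0.2; alpha 0.05; power 0.8; one-sample comparison; n = 98 at three months. **From Statistical analyses, Step 2:** about 353. **Not stated, so varied here:** sidedness, SD scale, and pre-post correlation r.

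**1. Attempt to reproduce 98, taking 0.2 as mean change divided by SD of change.**
Normal approximation: n = ((z_alpha + z_power) / d)².
- Two-sided: ((1.960 + 0.842) / 0.2)² = 196.2, so 197.
- One-sided: ((1.645 + 0.842) / 0.2)² = 154.6, so 155.

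Exact noncentral t with n − 1 degrees of freedom:
- Two-sided: 199 (power 0.802 at 199).
- One-sided: 156.

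Neither version gives 98.

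**2. Power at n = 98 for d = 0.2 (exact t).**
- Two-sided: 0.50.
- One-sided: 0.63.

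Two-sided, the smallest standardised change that 98 detects with power 0.8 is about 0.286. One-sided it is about 0.253.

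**3. Can another reading of 0.2 give 98?** If 0.2 is in raw-score SD units, with equal SDs at both times, the standardised change is d_z = 0.2 / √(2(1 − r)).

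| r | d_z | n, two-sided t | Power at 98, two-sided | Power at 98, one-sided |
|---|---|---|---|---|
| 0.40 | 0.183 | 238 | 0.43 | 0.56 |
| 0.50 | 0.200 | 199 | 0.50 | 0.63 |
| 0.60 | 0.224 | 159 | 0.59 | 0.71 |
| 0.70 | 0.258 | 120 | 0.72 | 0.81 |
| 0.75 | 0.283 | 101 | 0.79 | 0.87 |

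At r = 0.75 the two-sided normal approximation gives 196.2 × 2(1 − 0.75) = 98.1, which is the article's figure to rounding. The correlation at which 98 reaches power 0.8 by exact t is r = 1 − (0.2 / d_z)² / 2:
- Two-sided: 1 − (0.2 / 0.2858)² / 2 = 0.755.
- One-sided: 1 − (0.2 / 0.253)² / 2 = 0.69.

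Other routes come near 98 only by adding or changing an input. A variance factor of (1 − r²) with r = 0.7 gives 100.1. A two-sample comparison at d = 0.4 gives 99 per arm. Cohen's f of 0.2 over two occasions with zero correlation gives 101.

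**4. Power at the planned size.** With d = 0.2 two-sided and n = 353, power is 0.963.

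**The case against.** The strongest defence is that 98 rests on an unstated assumption and is not a slip. Normative scores are cross-sectional raw scores, so scaling 0.2 by the raw-score SD is a natural reading, and r = 0.75 then gives 98.1. A reader might infer from 98 being half of 196 that a factor of two was dropped. That inference is not supported, because r = 0.75 under raw-score scaling also halves 196. For the same reason, calling the figure wrong by a factor of two goes too far: that ratio holds only for a two-sided test with 0.2 scaled by the SD of the change. One-sided, the shortfall is 156 / 98, about 1.6.

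A reader might also say that 98 works only with a correlation of at least 0.755. That holds two-sided. The article does not fix sidedness and its hypothesis is one of improvement; one-sided, about 0.69 suffices.

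Next, a condensed article may leave the SD scale and correlation to the full protocol, so their absence is not in itself a fault. This stands, but the article chose to publish a complete power sentence, and its stated inputs do not yield its stated n when 0.2 is read as the standardised mean change. The normative-score basis supplies no pre-post correlation. The calculation also cites normative sources for several measures, so the required correlation would have to hold on each of them.

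Finally, the harm is remote. A larger sample is promised, no decision rule uses 98, and Step 3 needs about 120 randomised parents drawn from Step 2, which 98 at three months could not supply. This also stands, and it limits the severity.

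**Conclusion.** The point holds in this form: the Step 2 minimum of 98 at three months does not follow from effect size 0.2, alpha 0.05, power 0.8 and a one-sample comparison. With 0.2 as the standardised mean change, the requirement is 199 two-sided or 156 one-sided, and 98 gives power 0.50 or 0.63. The figure is recovered only with 0.2 in raw-score SD units and an unstated correlation of about 0.75 two-sided or about 0.69 one-sided.

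Severity is moderate. A reader might infer that Step 2 is underpowered as planned. The documents do not support that: about 353 in the analysis gives power 0.96 on the same reading of 0.2. It is equally tempting to add that 353 leaves room for about 44% attrition (1 − 199 / 353 = 0.44). That would require 353 to be the number recruited before loss. The article attaches it to the baseline to three-month analysis, so it may already be the number analysed. The fault is confined to the stated floor and its justification.

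**What to change.** Choose one of two changes to the Step 2 paragraph of the Sample size section.

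- **Correct the figure.** Replace 98 with 199 followed up at three months, stating two-sided alpha 0.05 and a standardised mean change of 0.2. Add that about 353 analysed gives power 0.96.
- **Keep 98 and state its basis.** Give the SD that scales 0.2, the sidedness, and the pre-post correlation used. Show the power at lower correlations: under raw-score scaling and two-sided testing, 0.50 to 0.72 for correlations of 0.5 to 0.7.

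In either case, leave out any statement about tolerable attrition unless 353 is confirmed as the number recruited before loss.

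The cost is a sentence or two of text. Design, analysis and recruitment target stay as they are.

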#### Step 3 active dissemination: parent information support group intervention

The data from the three-month follow-up assessment for Step 2 will constitute the baseline (or pre-group) data for Step 3. Participants in Step 3 will also complete an additional questionnaire at the first group session regarding their expectations of the group and what mental health support they might already be receiving. Medical records for the child of parents in Step 3 will be reviewed to record any hospital-based nursing or allied health staff involvement with the family.

On completion of the Information Support group, participants will be provided with the follow up questionnaire as part of the last group session. Follow up assessment of the group intervention will occur between April – September 2014. Participants in the waitlist control group will be completing the 6-month follow up assessment from baseline in Step 2 of the study at this time. This will provide the control comparison data to assess the additional impact of the group intervention, compared to receiving the booklet alone. The waitlist control group will then proceed to participate in the group intervention. All participants in Step 3 will be scheduled to complete a final follow up (single-group) assessment six months after they attended the group. This will provide repeated measures pre-post data regarding the longer-term efficacy of the group intervention. Participants will receive a prompt letter regarding six month follow up and approximately two weeks later a phone call, giving them the option to complete the questionnaire over the phone, online or receive a hard copy in the mail. Six-month follow up of participants in Step 3 is anticipated to occur between October 2014 – March 2015.

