#### Step 3 active dissemination: information support group intervention

Initial analyses will use demographic data to compare the characteristics of participants who agree to participate in Step 3 compared to those who decline to participate in this step of the project (despite meeting eligibility criteria, i.e. K10 > 15). Differences in responses according to demographic variables on the construct measures of interest (K10, FAD, family belief systems and MOSSSS) will also be analysed using oneway ANOVAs.

To examine the additional impact of the information support group intervention, relative to the wait-list control group (who will have only received the booklet intervention), an analysis of covariance will examine changes in mean scores on the outcome measures from baseline to post-intervention follow-up according to Group (n ≈ 60) versus Waitlist (n ≈ 60) allocation. To account for participant deviations from the protocol (such as dropout or failure to sufficiently participate in the group intervention), two analyses will be conducted. Data will be analysed using the intention-to-treat principle, which will assume all participants randomised to the intervention or waitlist group completed the study as per the research design and a per-protocol analysis will include only those participants who participate in a minimum of two-thirds of the intervention (Porta et al. 2007). Following post-intervention follow-up data collection, the waitlist group will complete the information support group intervention, and complete the post-intervention follow up. All group-based intervention participants will complete a six-month follow-up assessment. Thus, to test for sustained change, a second analysis will compare mean scores at baseline, post-intervention and six-month follow up on the same outcome measures for all participants in Step 3 of the intervention (n ≈ 120). There will be no treatment allocation variable in this second analysis. Further analyses will adjust for baseline characteristics to control for any confounding effects.

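### Step 3 power of at least 0.8 is tied to 60 per group at the pre-group baseline, and is not shown for the number who will have post-intervention outcome data

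*Protocol article*

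**What the plan says.** The Step 3 paragraph of Sample size reads: "A sample size of approximately 120 (60 per group) participants at the three month follow up assessment will allow detection of a significant difference". The claimed power is 0.8 or higher, and the calculation is described as "using an alpha level of 0.05 in a two-sample comparison of the group condition and control condition on the outcome measures". The hypothesised effects are 0.5 for parents who receive the booklet and the group, and 0.3 for controls.

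Data collection procedures, Step 3, fixes what the three-month assessment is: "The data from the three-month follow-up assessment for Step 2 will constitute the baseline (or pre-group) data for Step 3". It is also the assessment at which the K10 score determines eligibility, before invitation and random allocation (Participants and recruitment, Step 3). The outcome follows later. The group arm completes it at the last group session, and the waitlist arm at the six-month Step 2 assessment.

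Statistical analyses, Step 3, describes the randomised comparison as one of "changes in mean scores on the outcome measures from baseline to post-intervention follow-up according to Group (n ≈ 60) versus Waitlist (n ≈ 60) allocation". The later single-group analysis of sustained change is given about 120 participants.

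On loss, the Intervention section says that "participation in face-to-face groups can be low and attrition rates high", and Statistical analyses names dropout as a deviation to be handled. The only attrition allowance is in the Step 2 paragraph of Sample size. There, more parents than the minimum of 98 are to be recruited, to cover attrition and to supply enough parents eligible for Step 3.

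**The concern.** Power depends on how many parents have an outcome score. The article attaches its power to a count at the point where Step 3 begins. It then repeats that count, approximately, at the two later analyses. Step 2 is handled differently in the same section: its minimum of 98 is counted at the assessment where the outcome is measured, and over-recruitment is mentioned. The Step 3 statement does neither for the period after randomisation.

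Step 3 is the only randomised comparison in the programme. If its result is null, readers will judge it against the printed power of at least 0.8. That is misleading if the figure does not belong to the sample analysed.

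**Working it through.** **Inputs from the article.** Alpha 0.05 (sidedness not stated), power at least 0.8, 60 per arm, 1:1 allocation, effects of 0.5 and 0.3 by arm.

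**Assumptions.** Two-sided test; two-sample t-test as the plain form of a two-sample comparison; loss of 10%, 20% or 30%, equal in both arms. The article gives no loss rate.

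**Formula.** By normal approximation, power = Φ(d·√(n/2) − 1.96), where d is the between-arm difference in SD units and n the number per arm with outcome data. The t-test version uses a noncentral t with 2n − 2 degrees of freedom and noncentrality d·√(n/2).

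**The article's own figure, no loss, n = 60**
- Difference implied by the two effects: 0.5 − 0.3 = 0.2. Then 0.2 × √30 = 1.095, and Φ(1.095 − 1.96) = 0.19. About 393 per arm would be needed for 0.8.
- If 0.5 alone is taken as the between-arm difference: 0.5 × √30 = 2.739, and Φ(0.779) = 0.782. The t-test gives 0.775, and 64 per arm would be needed.
- One-sided with 0.5: 0.86.

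The printed figure is therefore nearly reached two-sided if 0.5 is the between-arm difference, and is far from reached at 0.2.

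**Effect of loss, difference 0.5, two-sided**

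| Assumed loss | n per arm | d·√(n/2) | Normal approximation | t-test |
|---|---|---|---|---|
| 0% | 60 | 2.739 | 0.782 | 0.775 |
| 10% | 54 | 2.598 | 0.738 | 0.731 |
| 20% | 48 | 2.449 | 0.688 | 0.679 |
| 30% | 42 | 2.291 | 0.630 | 0.620 |

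Cost of loss alone, by t-test: 0.775 − 0.731 = 0.044 at 10%, and 0.775 − 0.620 = 0.155 at 30%, so about 4 to 16 points. A further 2.5 points (0.80 − 0.775) are missing before any loss.

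**Effect of loss, difference 0.2.** At n = 48, 0.2 × √24 = 0.980, and Φ(0.980 − 1.96) = 0.16. Against 0.19 with no loss, 20% loss costs about 3 points.

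**Detectable difference at power 0.8 (t-test).** 0.52 SD at 60 per arm and 0.58 SD at 48 per arm.

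**Allowing for ANCOVA.** With a baseline-outcome correlation r, d is replaced by d/√(1 − r²). For d = 0.5 and an assumed r = 0.5, this is 0.5/√0.75 = 0.577. Power (t-test form) is then 0.88 at 60 per arm, 0.80 at 48 and 0.74 at 42.

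**The case against.** The strongest reply is that the time label is merely loose. A between-arm outcome comparison cannot be made at a pre-group baseline, so the 60 may have been meant as the number with outcome data, about three months after Step 3 entry. The text gives this no support, because it calls the Step 3 follow-ups post-intervention and six-month. Even on that reading, the number to be randomised would be unstated.

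A second reply is that an article may leave a dropout allowance to the full protocol. That would answer a bare omission. Here, however, the article prints a number, a time point and a power that do not fit its own schedule.

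Several objections do stand, and they limit the point:
- A reader might infer that the plan declares zero loss. It does not. The later figures are approximate and can be read as the randomised set, because the intention-to-treat analysis treats everyone randomised as having completed. That reading supplies no outcome data for parents who are lost.
- The attrition remark concerns face-to-face groups, and the mixed face-to-face and online format is offered as the response to it. It does not establish any particular rate of missing questionnaires, least of all in the waitlist arm.
- A reader might put the shortfall from attrition at 7 to 18 points below 0.8. That range includes the 2.5 points already missing at full retention.
- The article names neither a t-test nor a sidedness. One-sided, with a difference of 0.5, power would still be about 0.81 at 15% loss.
- The planned analysis is ANCOVA. With the assumed correlation of 0.5 it would hold about 0.80 at 20% loss. The sample-size paragraph claims no such gain.

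**Conclusion.** The mismatch is firm: the stated power belongs to a count at the Step 3 baseline, and no loss after randomisation is allowed for before the comparison it is meant to support. Power of at least 0.8 is therefore not shown for the parents who will have outcome data.

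The size is conditional. On a two-sided t-test with a difference of 0.5, assumed losses of 10% to 30% bring power from 0.775 to between 0.73 and 0.62. The documents do not support a specific shortfall, because they give no loss rate and the covariate-adjusted analysis could recover part of the loss.

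Nor is attrition the main weakness of the calculation. At the 0.2 difference implied by the stated effects, power is 0.19 with full retention, and correcting the count would not repair that. The point merits a correction to the text; it does not show that attrition by itself makes the trial inadequate.

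**What to change.** In Sample size, Step 3:
- tie the number to participants with outcome data at the post-intervention follow-up;
- state the loss assumed between randomisation and that assessment;
- name the between-arm difference and the test used, including sidedness and any baseline correlation credited to ANCOVA;
- restate the power, or the detectable difference, for the number then analysed. For example, 48 per arm after an assumed 20% loss detects 0.58 SD, unadjusted, with power 0.8.

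In Statistical analyses, Step 3, replace the repeated 60, 60 and 120 with separate expected numbers randomised, analysed at post-intervention and analysed at six months.

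The cost is wording in two sections and a less favourable stated power. Added recruitment is not part of this fix. If the sponsor instead wished to keep 60 evaluable per arm, the number to randomise would be 60/(1 − loss): 67, 75 or 86 per arm at 10%, 20% or 30%. Restating power without also settling the between-arm difference would only replace one unsupported figure with another.

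### Step 3 sample size: the claimed power of at least 0.8 with 60 per arm does not follow from the hypothesised effects of 0.5 and 0.3, which imply a between-arm difference of only 0.2 SD

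*Protocol article*

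**What the plan says.** The Step 3 paragraph of the Sample size section in the protocol article gives all the inputs.

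- Effects: "Effect sizes of 0.5 and 0.3 were hypothesised as a result of receiving the booklet intervention and participating in the information support group intervention". The end of that sentence assigns the two values in order, the second to the control condition. So 0.5 belongs to booklet plus group and 0.3 to the control condition.
- Allocation: "the sample size will be divided randomly and equally between the group condition and the waitlist control condition".
- Test: "using an alpha level of 0.05 in a two-sample comparison of the group condition and control condition on the outcome measures". Sidedness is not stated.
- Size and claim: "A sample size of approximately 120 (60 per group) participants at the three month follow up assessment will allow detection of a significant difference", "with a power of at least 0.8".

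The Step 3 part of Statistical analyses describes the analysis as an ANCOVA of the change in mean scores from baseline to post-intervention, "according to Group (n ≈ 60) versus Waitlist (n ≈ 60) allocation". It describes the target as the added impact of the group over controls who have had the booklet alone. No baseline-outcome correlation is given for Step 3.

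**The concern.** The control arm is not assumed to stand still. It is credited with an improvement of 0.3 from the booklet, and the group arm with 0.5 from booklet and group together. A test of the group's added effect sees only the gap between the two, 0.2 SD. Sixty per arm is the order of size usually needed for a difference near 0.5 SD, so the size and the effects in one paragraph do not belong to the same calculation.

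Step 3 is the only randomised comparison in the study, and the Discussion relies on it for a rigorous evaluation of the support group. A reader who accepts the stated power will think the trial well able to detect its hypothesised benefit when, on its own inputs, it probably is not.

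**Working it through.** **Inputs.** From the Sample size section: effects 0.5 and 0.3, 60 per arm, 1:1 allocation, alpha 0.05, claimed power at least 0.8. Assumed here: effects are in SD units, the test is two-sided, and the baseline-outcome correlation r lies between 0.5 and 0.8. Power is from the noncentral t distribution unless noted.

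**1. Trying to reproduce the plan's figure.** Unadjusted two-sample comparison, 60 per arm:

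| Between-arm difference | Power, two-sided | Power, one-sided | n per arm for 0.80, two-sided |
|---|---|---|---|
| 0.2 (0.5 − 0.3) | 0.192 | 0.289 | 394 |
| 0.3 | 0.371 | 0.496 | 176 |
| 0.5 (control arm unchanged) | 0.775 | 0.859 | 64 |

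The contrast the paragraph implies, 0.2, does not reproduce 0.8 with either sidedness. Only a difference of 0.5 comes close, and that sets aside the 0.3 given to controls. That the figure arose in this way is an inference; the article does not say so.

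**2. Check by hand for 0.2.** n per arm = 2 × (1.960 + 0.842)² / 0.2² = 2 × 7.849 / 0.04 ≈ 393 (394 with the t correction). In reverse, the standardised distance is 0.2 × √(60/2) = 1.095, and power ≈ Φ(1.095 − 1.960) = Φ(−0.865) ≈ 0.19.

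**3. With the planned ANCOVA.** Baseline adjustment multiplies the SD by √(1 − r²), so the effective difference is 0.2/√(1 − r²):

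| r (assumed) | √(1 − r²) | Effective difference | Power, two-sided, 60 per arm | Difference detectable with power 0.80 |
|---|---|---|---|---|
| 0 | 1.000 | 0.200 | 0.19 | 0.52 |
| 0.5 | 0.866 | 0.231 | 0.24 | 0.45 |
| 0.6 | 0.800 | 0.250 | 0.27 | 0.41 |
| 0.7 | 0.714 | 0.280 | 0.33 | 0.37 |
| 0.8 | 0.600 | 0.333 | 0.44 | 0.31 |

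The last column is 0.516 × √(1 − r²), where 0.516 SD is the difference detectable unadjusted with 60 per arm.

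**4. What r would rescue the claim?** Set 0.2/√(1 − r²) = 0.516. Then r = √(1 − (0.2/0.516)²) ≈ 0.92. A one-sided ANCOVA would still need about 0.90.

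**5. A correlation implied elsewhere in the section.** Step 2's 98 participants for an effect of 0.2 fit a paired comparison if 98 = 7.849 × 2(1 − r)/0.04. This gives 2(1 − r) ≈ 0.50 and r ≈ 0.75. Carried into Step 3, that r gives power of about 0.34 with change scores and 0.38 with ANCOVA, still under half the claimed figure.

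**6. If 0.5 was meant as the between-arm difference.** Unadjusted power is 0.775. With ANCOVA, 0.80 is reached once 0.5/√(1 − r²) = 0.516, that is r = √(1 − (0.5/0.516)²) ≈ 0.25. At r = 0.5 power is 0.88.

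**The case against.** The best defence is that 19% is not the power of the planned test. The plan is an ANCOVA, the correlation and sidedness are unstated, and the hypothesis is worded as a direction (greater improvement). This stands, so the result has to be given as a range. It does not save the claim: two-sided ANCOVA reaches 0.44 at r = 0.8, and one-sided ANCOVA at the same r reaches 0.57.

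Four stronger readings are tempting, and the document does not support them.

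- *Sixty per arm should be 64.* This holds only for a 0.5 SD difference tested two-sided without adjustment. With the planned ANCOVA, 60 per arm suffices for 0.5 SD once r is about 0.25, and the total is given only as approximately 120.
- *No loss after randomisation is allowed for.* The Intervention section does warn that "participation in face-to-face groups can be low and attrition rates high", but it then adopts a mixed face-to-face and online format for that reason. The three-month time point attached to the 120 is ambiguous: it is the Step 3 baseline under Data collection procedures, yet the Step 2 paragraph uses the same phrase for the outcome assessment. The 120 may be those assessed at outcome. The article gives no expected loss rate either.
- *The trial has a one-in-five chance of success.* That is the bottom of the range, for the unadjusted test only.
- *A null result will be taken as evidence against the group.* Nothing in the article says how a non-significant result would be read.

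**Conclusion.** The point holds in this form: the stated power does not follow from the stated effects. For 0.5 versus 0.3, 60 per arm gives power of about 0.19 unadjusted and about 0.24 to 0.44 with ANCOVA, against a claim of at least 0.8. The conclusion assumes effects in SD units, two-sided alpha 0.05, 60 per arm analysed, and r between 0.5 and 0.8. Only r is a free choice that matters much, and it would have to be about 0.92 to make the claim true. The reading of 0.3 as the control arm's own improvement comes from the article's wording and from its description of controls as having received the booklet. The finding does not extend to the adequacy of 60 per arm for a 0.5 SD difference, to attrition, or to how results will be interpreted.

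**What to change.** Reword the Step 3 sample size paragraph; enrolment need not change. Suggested text:

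*With 60 per arm analysed, the trial has 80% power at two-sided alpha 0.05 for a between-arm difference of about 0.52 SD unadjusted, or about 0.45 to 0.31 SD with baseline-adjusted ANCOVA at a baseline-outcome correlation of 0.5 to 0.8. For the hypothesised effects of 0.5 and 0.3 its power is about 0.19 unadjusted and 0.24 to 0.44 with ANCOVA.*

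Also state the between-arm difference, sidedness and correlation that were actually used. If 0.5 was meant as the difference between arms, say so and remove or reconcile the 0.3 for controls. Sixty per arm then gives 0.775 unadjusted and at least 0.80 with ANCOVA once the correlation is about 0.25.

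The cost is one paragraph and, unless 0.5 was the intended difference, a less favourable stated power.
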